### Confidentiality {27}

The investigators affirm and uphold the principle of the participant’s right to privacy and will comply with the applicable privacy laws. The anonymity of the participants will be guaranteed when presenting the data at scientific meetings or publishing them in scientific journals. Individual medical information obtained as a result of this trial will be considered confidential and will not be disclosed to third parties. Direct access to not encrypted source documents will be permitted for authorized third parties for purposes of monitoring, audits, and inspections. The trial staff will have access to the trial data based on authorization by the principal investigator. Confidentiality will be established by utilizing identification codes to link participants with trial data. The identification codes will not contain name, initials, date of birth, or any other personal identification numbers (e.g., social security number, patient identification number, etc.). The list with the assigned trial identification codes and minimal personal information (i.e., name, date of birth) will be stored in a locked cabinet at the trial site. All CRFs and data collection files will be identified with the trial code only. After trial closure, all trial data will be stored in a locked archive room with limited access for 10 years.

### Plans for collection, laboratory evaluation, and storage of biological specimens for genetic or molecular analysis in this trial/future use {33}

All processing of biological specimens will be done with encrypted samples (blood and urine). The samples from each assessment time point will be transferred for processing to the SwiSCI Biobank, which has been audited and certified by the Swiss Biobanking Platform (SBP). The processing of the samples will be done preferably by a team of two persons (preferably) according to validated workflows and SOPs, starting with the most perishable sample (urine), in order to ensure the shortest possible processing (needle-to-freezer) time. A biobanking software (FreezerPro Brooks, Chelmsford, MA, USA) will be used for documentation as well as sample and aliquot tracking. Samples will be accessed and withdrawn according to validated procedures and analyzed according to the trial protocol. Any unused samples will be stored for at least 5 years after the end of the trial.

## Statistical methods

### Statistical methods for primary and secondary outcomes {20a}

All the data of randomized trial participants will be analyzed blinded and according to an intention-to-treat basis. This is a feasibility trial, and thus, descriptive statistics will be used. All outcome measures will be presented as point estimates and 95% confidence intervals. Differences in clinical and laboratory outcome measures between the two treatment groups will be evaluated based on confidence intervals.

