## Trial design {8}

This is a randomized, placebo-controlled, mono-centric pilot trial with two parallel groups of 12 trial participants each (1:1 allocation). Allocation will be determined by block-randomization stratified according to sex. The reason for stratification according to sex is the higher risk of UTIs in women with SCI [16]. Trial participants will receive the intervention for 90 days and will be followed up for 3 months thereafter.

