### Sample size {14}

A total of 24 participants will be included based on the rule of thumb of 12 participants per treatment arm in pilot studies suggested by Julious and Owen [17]. The sample size will be sufficient to evaluate the feasibility of a main trial which is the primary objective of this pilot trial. If more than 6 participants in a treatment arm terminate the trial prematurely, additional participants will be recruited until at least 6 have completed the trial protocol.

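### The stated arm comparison declares no use of the sex strata or baseline laboratory values; run that way it gives up precision, and the many laboratory intervals are not labelled exploratory

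*Protocol article*

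**What the plan says.** Under *Statistical methods for primary and secondary outcomes {20a}* the protocol article states: "This is a feasibility trial, and thus, descriptive statistics will be used". It continues: "All outcome measures will be presented as point estimates and 95% confidence intervals". The arm comparison is then fixed in one sentence: "Differences in clinical and laboratory outcome measures between the two treatment groups will be evaluated based on confidence intervals". No model, covariate, multiplicity statement or lead laboratory marker is named.

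*Trial design {8}* says: "Allocation will be determined by block-randomization stratified according to sex". It gives the motive: "The reason for stratification according to sex is the higher risk of UTIs in women with SCI". Under *Secondary outcomes: clinical measures* and *Biological outcomes*, the urinary status, blood counts, IgA and cytokines are measured at baseline, treatment end and trial end.

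*Sample size {14}* gives the size: "A total of 24 participants will be included based on the rule of thumb of 12 participants per treatment arm in pilot studies". If more than 6 in an arm stop early, "additional participants will be recruited until at least 6 have completed the trial protocol".

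**The concern.** There are two separate issues.

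**Precision.** Stratified allocation balances sex between arms, so sex adds nothing to the true variance of the arm difference. An analysis without sex still leaves the between-sex spread in its error estimate, so the interval is too wide for any outcome that sex predicts. By the article's own reasoning, the UTI count is such an outcome. Likewise, a comparison of follow-up values alone leaves the baseline sample unused. With 12 per arm, precision is scarce, and one objective is to collect data for sizing the main trial.

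**Reading of the intervals.** The article calls the analysis descriptive and then says that differences are evaluated from intervals. A reader could take that as checking whether each interval excludes zero. With dozens of laboratory measures, some would do so by chance. The Discussion presents the immune and microbiome responses as the trial's distinctive feature, so such results may attract attention.

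**Working it through.** **1. Size and basic width.** 2 × 12 = 24 reproduces the stated total. The unadjusted half-width is t(0.975, 22) × √(2/12) = 2.074 × 0.408 = 0.85 SD. At the floor of 6 completers per arm it is t(0.975, 10) × √(2/6) = 2.228 × 0.577 = 1.29 SD.

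**2. Leaving out sex.** Assumptions: a continuous outcome, 16 men and 8 women balanced within sex, and a sex effect of 1 SD. The article gives no enrolled sex mix; its allocation list has 20 male and 12 female places.
- True variance of the difference: (2/12)σ², because sex cancels.
- Error variance estimated without sex: 1 + [24 × (1/3) × (2/3)]/22 = 1 + 5.33/22 = 1.242 (in units of σ²).
- Width factor: √1.242 = 1.11.

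Simulation agrees:

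| Sex effect | Coverage without sex | Mean width without / with sex |
|---|---|---|
| 0.5 SD | 95.6% | 1.725 / 1.678 = 1.03 |
| 1 SD | 97.1% | 1.867 / 1.678 = 1.11 |
| 1.5 SD | 98.5% | 2.084 / 1.678 = 1.24 |

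With sex in the model, coverage is 95.0%.

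**3. Adding sex and baseline.** The article gives no correlation r between baseline and follow-up, so a range is shown. Entries are simulated interval width, ANCOVA on sex and baseline divided by unadjusted, with about a quarter of participants women (3 of 12 per arm; 2 of 6 in the smaller case):

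| r | 12 per arm, no sex effect | 12 per arm, 1 SD | 6 per arm, no sex effect | 6 per arm, 1 SD |
|---|---|---|---|---|
| 0 | 1.03 | 0.94 | 1.09 | 0.97 |
| 0.3 | 0.98 | 0.90 | 1.04 | 0.93 |
| 0.5 | 0.89 | 0.81 | 0.95 | 0.84 |
| 0.7 | 0.74 | 0.67 | 0.78 | 0.69 |

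With 8 women of 24 and a 1 SD sex effect, the narrowing at 12 per arm is about 8% at r = 0 and 20% at r = 0.5.

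The closed form √(1 − r²) × t(0.975, 20)/t(0.975, 22) gives 0.871 at r = 0.5 and 0.718 at r = 0.7. It omits the cost of chance baseline imbalance, so the simulated values are used here.

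**4. Number of laboratory intervals.** Named measures: 6 urinalysis + 8 blood count + 6 differential + 2 IgA + 11 cytokines = 33. Counting both cytokine assays gives 33 + 11 = 44. At two post-baseline visits these become 66 and 88. The microbiome is left out.

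Expected exclusions of zero under no effect: 33 × 0.05 = 1.65 and 88 × 0.05 = 4.4. Correlation leaves this mean about unchanged but spreads the count. For 88 intervals, the chance of three or more is 0.82 if independent and 0.40 at a common correlation of 0.5.

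**5. The two issues have different remedies.** An adjusted interval still excludes zero in about 5% of null comparisons, so 4.4 of 88 remains the expectation. Leaving out a 1 SD sex effect (a quarter women) lowers the rate to about 3.1–3.5%, that is 88 × 0.031 = 2.7 to 88 × 0.035 = 3.1.

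**The case against.** The strongest reply is that the article never says the intervals are unadjusted. A reader might infer that the trial has chosen to ignore sex and baseline. The text does not support that: it names no model, and a fuller protocol or analysis plan may name one. This stands, and the point is therefore conditional. The word descriptive makes an unadjusted comparison a plausible reading but does not establish it.

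The gain also rests on figures the article does not give. The rationale for sex concerns UTI risk, not laboratory values, and no correlation is reported. This stands too: with weak correlation and no sex effect, adjustment costs a little width.

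A reader might further infer that several laboratory intervals will exclude zero and then shape the main trial. Neither part is supported. The figure of 4.4 is an average under no effect, needs both assays and both visits to be counted, and concerns related markers. The article ties going forward to feasibility, makes the randomization rate the primary outcome, and attaches no decision to any laboratory result.

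Finally, estimates with 95% intervals are ordinary pilot output, and no test or threshold is stated. That is fair: the wording is open to two readings and is not a formal contradiction.

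**Conclusion.** The point holds in conditional form. The stated comparison declares no use of the stratification factor or of the baseline laboratory values. If it is run that way:

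- An outcome on which sex is prognostic gets a conservative interval, with about 97% coverage for an assumed 1 SD effect. This was computed for a continuous outcome. For the UTI rate ratio it shows the direction only, and no width gain was computed.
- Laboratory intervals are wider than needed once baseline and follow-up correlate at about 0.5 or more. At 12 per arm with no sex effect, adjustment narrows them by 11% at 0.5 and 26% at 0.7.
- The downside of adjusting is about 3% extra width at 12 per arm, or 9% at 6, if neither covariate is prognostic.

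Separately, the article leaves open how 33 to 88 laboratory intervals are to be read. These are secondary comparisons in a feasibility trial, so this is a worthwhile low-cost improvement and no threat to the primary objective.

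**What to change.** 1. Estimate differences in continuous laboratory measures by ANCOVA with treatment, sex and the baseline value, on the log scale for IgA and cytokines. Keep dipstick items descriptive.
2. Estimate the UTI rate ratio from a count model with treatment and sex, and log(days observed) as offset.
3. Say in the statistical methods section that the laboratory intervals are exploratory, are not adjusted for multiplicity, and are not read as evidence for or against an effect. Whether to name a lead marker, and which one, is for the sponsor.

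If a fuller plan already contains items 1 and 2, only item 3 is needed. The cost is a few sentences and lines of code, settled before unblinding, with no new data. With 6 completers per arm, the ANCOVA leaves 12 − 4 = 8 residual degrees of freedom, which is the source of much of the 9% worst-case widening.

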### Interim analyses {21b}

This is a feasibility trial, and thus, no interim analyses will be performed.

### Methods for additional analyses (e.g., subgroup analyses) {20b}

This is a feasibility trial, and thus, there will be no subgroup analyses.

### Methods in analysis to handle protocol non-adherence and any statistical methods to handle missing data {20c}

All available data will be included for intention-to-treat analysis. Missing data will not be imputed.

### Plans to give access to the full protocol, participant-level data, and statistical code {31c}

Access to the full protocol, participant-level data, and statistical code will be given upon reasonable request to the corresponding author.

## Oversight and monitoring

### Composition of the coordinating center and trial steering committee {5d}

There is no coordinating center or trial steering committee.

### Composition of the data monitoring committee, its role, and reporting structure {21a}

This is a mono-centric pilot trial evaluating the feasibility of a main trial investigating an approved medicinal product with a low-risk profile. Thus, there is no data monitoring committee.

### Adverse event reporting and harms {22}

Treatment side effects are collected from self-report questionnaires fortnightly during the treatment period.

All SAEs are collected and documented from the start of the trial treatment until 7 days after completing or terminating the treatment (safety follow-up time). Any suspected unexpected (not consistent with product information) serious adverse reaction (SUSAR) will be reported to the ethics committee within 15 days (events resulting in death within 7 days) of becoming aware of the event.

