### Provisions for post-trial care {30}

There are no provisions for post-trial care, as there is no risk of harm as a result of the trial intervention after intervention termination and beyond follow-up period.

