### Participant timeline {13}

The schedule of enrolment, interventions, assessments, and visits for participants is shown in Fig. 1. Eligible patients will be approached regarding trial participation after admission for primary rehabilitation as soon as their physical and mental condition allows. The trial intervention will commence not later than 56 days after SCI has occurred. Prior to intervention start, blood and urine samples will be taken as well as at the end of the intervention and 3 months after intervention termination (Fig. 1). The trial intervention will last 90 days. During the intervention and follow-up period (3 months), the occurrence of UTIs, symptoms, and treatment will be recorded. At the trial end, participants will fill out a questionnaire regarding their experiences during the course of the trial. In participants who prematurely stop the trial, a safety follow-up period of 7 days will be observed to monitor the occurrence of SAEs.

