#### Clinical outcomes

During the intervention period, trial participants will complete a self-developed paper questionnaire regarding UTI symptoms and treatment side effects every 2 weeks. The following UTI symptoms are listed: fever/shivering; new or increased urinary incontinence/leaking, increased urgency, increased catheterization frequency; increased spasticity; malaise, feeling sick, fatigue; cloudy, foul-smelling urine; abdominal/lower back/kidney pain, pain during bladder voiding; and goose bumps, increased sweating. Participants have the possibility to list any other symptoms experienced. An event is counted as a symptomatic UTI if at least one bladder symptom (new or increased urinary incontinence/leaking, increased urgency, increased catheterization frequency, pain during bladder voiding) and another symptom have been reported together with a positive urine analysis result (leucocytes, nitrite) and a growth of ≥10,000 cfu/ml in the urine culture (sample collected by *via naturalis*).

The following side effects are listed: headache, abdominal pain, nausea, vomiting, diarrhea, and heartburn. Participants have the possibility to list any other side effects experienced. In the event of a symptomatic UTI, data from clinical routine assessments (i.e., urinary status and urine culture results) and the chosen treatment will be collected from the electronic medical chart file and recorded in an eCRF.

During the follow-up period, trial participants will complete a self-developed paper questionnaire regarding UTI symptoms (same as above), assessments (dip stick and urine culture), and treatment fortnightly. In the event of a symptomatic UTI in still hospitalized trial participants, data from clinical routine assessments (i.e., urinary status and urine culture results) and the chosen treatment will be collected from the electronic medical chart file and recorded in an eCRF.

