### Plans to promote participant retention and complete follow-up {18b}

Trial participants will remain hospitalized during the treatment period (see eligibility criteria). If a trial participant is discharged before completion of the trial, telephone interviews will be planned to collect outcome measures regarding UTIs, in case the participant does not return the self-report questionnaires.

In participants who discontinue or deviate from intervention protocols, all outcome data as per protocol will be collected as long as participants stay in the trial. In case of premature trial termination, clinical routine data regarding UTIs will be collected, if participants have not rejected the use of health-related data and samples for research purposes (general consent).

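### SAE collection stops 7 days after each participant's last dose, leaving about 46% of the observation period uncovered and giving those who stop treatment early a shorter SAE window

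*Protocol article*

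**What the plan says.** All references are to the protocol article.

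- *Trial design {8}*: "Trial participants will receive the intervention for 90 days and will be followed up for 3 months thereafter".
- *Adverse event reporting and harms {22}*: "All SAEs are collected and documented from the start of the trial treatment", and the collection runs "until 7 days after completing or terminating the treatment (safety follow-up time". On milder events: "Treatment side effects are collected from self-report questionnaires fortnightly during the treatment period". The side-effect entry under *Secondary outcomes: clinical measures* has the same limit.
- *Participant timeline {13}*: "In participants who prematurely stop the trial, a safety follow-up period of 7 days will be observed to monitor the occurrence of SAEs".
- *Plans to promote participant retention and complete follow-up {18b}*: for participants who discontinue or deviate from the intervention, "all outcome data as per protocol will be collected as long as participants stay in the trial".
- *Clinical outcomes* (under {18a}): "During the follow-up period, trial participants will complete a self-developed paper questionnaire regarding UTI symptoms". These forms are fortnightly and also cover UTI assessments and treatment. Blood cell count, white cell differential and urine analysis are repeated at trial end.
- *Criteria for discontinuing or modifying allocated interventions {11b}*: treatment ends on withdrawal of consent, on an SAE related to the intervention, or when an exclusion criterion is present.
- *Statistical methods {20a}*: all randomised participants are analysed by intention to treat, with descriptive statistics and confidence intervals.

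**The concern.** Two features matter.

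First, harm is sought over a shorter period than benefit. UTIs, microbiome, cytokines and IgA are followed to trial end, so the design looks for effects of an immunomodulator beyond the last capsule. SAEs are sought for one week beyond it. A serious event in the last three months that is not a UTI has no planned route into the database. A serious UTI is recorded as a UTI but not as an SAE.

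Second, the SAE window closes on something that happens after randomisation and may be related to health. An SAE related to the intervention, or a newly present exclusion criterion such as immunosuppressant therapy or nephropathy, stops treatment and so starts the 7-day countdown, even if the participant stays in the trial and keeps supplying outcome data. If stopping is more frequent in one arm, that arm has less time in which an SAE can be recorded. A plain count would then make it look safer than it is.

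The stake is the quality of the harms data that this pilot passes on to the planned multi-centre trial.

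**Working it through.** **Inputs.** Treatment lasts 90 days ({8}). Follow-up is 3 months ({8}), taken as 90 to 92 days because a month is not defined. SAE collection ends 7 days after the last treatment day ({22}). Each arm has 12 participants ({8}). The protocol gives no coverage figure to reproduce and no expected discontinuation rate, so the stop days below are assumptions.

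**Completer.**
- Observation period: 90 + 90 = 180 to 90 + 92 = 182 days.
- SAE window: 90 + 7 = 97 days.
- Without SAE collection: 180 − 97 = 83 to 182 − 97 = 85 days; 83/180 = 46.1% to 85/182 = 46.7%.
- Without side-effect collection: 90/180 = 50.0% to 92/182 = 50.5%.

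**Stops treatment early, stays in the trial to the planned end.** SAE window = stop day + 7; uncovered share = 1 − window / (180 to 182).

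| Last treatment day (assumed) | SAE window | Observation without SAE collection |
|---|---|---|
| 90 (completer) | 97 days | 46.1–46.7% |
| 60 | 67 days | 62.8–63.2% |
| 30 | 37 days | 79.4–79.7% |
| 14 | 21 days | 88.3–88.5% |

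If follow-up instead ran 3 months from the actual stop, a day-30 stopper would be observed for 30 + 90 = 120 to 30 + 92 = 122 days. The window would still be 37 days, and the uncovered share 83/120 = 69.2% to 85/122 = 69.7%. The shortening does not depend on which clock applies.

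**Effect on an arm.** Twelve completers give 12 × 97 = 1,164 person-days of SAE collection. Each stop at day 30 removes 97 − 37 = 60 of them, or 60/1,164 = 5.2% of the arm's total.

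**The two 7-day rules side by side.** {22} starts the 7 days at the end of treatment; {13} starts them when a participant leaves the trial early. For someone who stops both on the same day the rules agree. For someone who leaves during follow-up they do not: under {22} collection has already closed, while under {13} it would run for 7 days after leaving. Read literally, a participant who leaves during follow-up gets a week of SAE monitoring that one who stays does not get.

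**Does {18b} extend the window?** It keeps outcome data coming after treatment stops. Side effects are a listed outcome, so those questionnaires may well continue to day 90. SAEs are not listed under *Outcomes {12}*, so {18b} does not clearly override {22}. The shortening is therefore firm for SAEs only.

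**The case against.** The strongest reply is that this is an openly stated choice for a feasibility pilot of an approved product, given according to its package leaflet and described as low-risk. On that view a longer window is a reviewer's preference. This stands to the extent that a 7-day window is not an error in itself. It does not answer why SAE time should depend on the last dose for people who remain under observation, or why two sections start it from different events.

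Several stronger readings are tempting, and the document does not support them:

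- *That the last three months yield no safety data.* They do yield some: trial-end blood counts, differential and urine analysis, and fortnightly reports of UTI symptoms (fever included), tests and treatment, with telephone interviews when forms are not returned. A late febrile UTI would largely be recorded, but without SAE classification and detail.
- *That the plan contains a biased between-arm SAE comparison.* None is stated. The comparability problem arises only if counts are set out by arm and discontinuation differs.
- *That the pilot promises a six-month safety statement.* No objective says so.
- *That {30} declares the follow-up period free of harm.* That sentence explains why no post-trial care is provided, and it goes on to refer to the time beyond follow-up.
- *That a longer window would sharpen the estimate of on-treatment risk.* It would mostly add time off the drug, in both arms, and 24 participants remain too few for a safety conclusion.

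An SAE that itself causes discontinuation falls inside the window; only later events are lost.

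**Conclusion.** The point holds as a limited weakness in harms collection. For a completer, about 46% of the observation period has no planned SAE collection and about 50% no planned side-effect collection. These shares assume full 90-day treatment and a follow-up of 90 to 92 days. The SAE window shortens with early discontinuation, to 37 days for an assumed stop at day 30. How much this would distort counts by arm cannot be estimated, because no discontinuation rates are given; if stopping is rare or balanced, the effect is small. The differing starting events in {13} and {22} need reconciling whatever length is chosen. The primary outcome, the randomisation rate, is not affected. This is a cheap improvement worth making.

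**What to change.** - In {22}, record SAEs for every randomised participant from first dose to the trial-end visit, whether or not treatment was stopped.
- Collect them through contacts the trial already makes: the fortnightly follow-up questionnaires (one added SAE question), the telephone interviews and the trial-end assessment.
- Bring {13} into line with {22}, so that one starting event and one end date apply, and state what applies to participants who leave the trial.
- Report SAEs by arm with the person-time observed. Keep events up to 7 days after the last dose as a separate on-treatment summary.
- State whether the treatment period for side-effect questionnaires means the planned 90 days or the time actually on treatment.

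If the sponsor keeps the present window, the minimum is to justify it, align the two sections and report SAEs per person-time by arm.

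The cost is small: wording changes, one questionnaire item, and a few more SAE forms in 24 participants, with no new visits. It is not zero. In follow-up, chart extraction for UTIs is planned only for participants still in hospital, so SAEs in discharged participants will need some outside records and source verification.
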